### Study protocol

The sequence of events of the randomized controlled trial is illustrated in Figure 6.

**Figure 6 F6:**
[figure not shown]
Flowchart of the clinical trial from recruitment to final assessment stages.

### Recruitment

Thirty participants will be consecutively recruite through advertisements in local newspapers and posters at the clinic offices of the Health Sciences Center, Winnipeg. Volunteers who contact the study staff will be screened according to the study participation criteria. Eligible participants will be issued a general information handout that explains the study purpose and the need to attend a baseline session, three training sessions and a final follow-up session at the Department of Physical Therapy, University of Manitoba. Written informed consent will be obtained from each participant.

### Baseline visit

An initial assessment will be conducted during the first visit, which will include the following: documentation of demographic information such as age, sex, occupation, diagnosis and disease duration; documentation of individual specific problems during specific tasks of daily living; observation of fine/gross finger abilities on handling different objects of daily life; and assessment of primary and secondary study outcomes.

### Randomization

After the baseline assessment, participants will be randomly allocated into one of the two groups. The randomization procedure will be as follows: sequence generation, the two groups will be generated with equal allocation ratio (1:1) by referring to a computer-generated group allocation –randomization will also be stratified, RA or OA condition wise, depending upon the number of participants being recruited; allocation concealment, allocation will be concealed in sequentially numbered, opaque, sealed envelopes and will be opened only after the participant details are written on the envelope; implementation, a staff member who is not involved with the trial will generate the random numbers, do the allocation concealment and keep them until the end of the study; and blinding, an independent assessor blinded to the group allocations will evaluate the study outcomes at baseline and at the end of the sixth week.

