### Sample size calculation

In this pilot trial, a formal sample size calculation was not carried out. Thirty participants [31] will be recruited and allocated into two groups throughout the data collection period.

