### Outcome measures

#### Primary outcome measure

The primary outcome measure will be the Arthritis Hand Function Test, an 11-item performance-based test that measures grip and pinch strength, dexterity, applied strength and dexterity in people with arthritis. Test–retest reliability of the Arthritis Hand Function Test measured by the intraclass correlation coefficient in 20 individuals with RA ranged from 0.53 to 0.96; inter-rater reliability ranged from 0.89 to 1.0. Test–retest reliability in 26 individuals with OA ranged from 0.7 to 0.96; inter-rater reliability ranged from 0.99 to 1.0 [38,39].

The peg-board dexterity test measures the time taken in seconds to place and remove nine pegs into the nine holes. Applied dexterity is the total time taken (seconds) to complete the following tasks: lacing a shoe, tying a bow, fastening/unfastening four buttons, fastening/unfastening two safety pins, cutting putty with a knife and fork, and manipulating coins into a slot.

Applied strength will be measured by the total number of soup cans lifted in a tray and the volume (ml) of water lifted in a pitcher.

Grip strength of the dominant hand will be clinically tested using a handheld dynamometer (Biometrics isometric hand dynamometer G100; Biometrics Ltd, Cwmfelingach, Gwent, UK). Grip strength will be recorded in kilograms and the best score out of the three consecutive trials will be used for analyses. Similarly, three-point pinch strength will be measured using a pinch meter (Biometrics precision pinch meter P200; Biometrics Ltd).

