### Statistical analysis plan

Normality of all data will be tested using Shapiro–Wilk’s test, based on which data will be appropriately described. Continuous variables will be reported as means ± standard deviation and noncontinuous variables will be reported as the median and interquartile range. Unpaired Student’s *t* test or Mann–Whitney U statistics will be used to compare the demographic variables and baseline outcomes between the two groups. Based on the data distribution of the study outcomes, grip strength, peg-board dexterity, applied dexterity and applied strength (Arthritis Hand Function Test items), DASH and number of exercise sessions completed in 6 weeks, changes over time (pre to post intervention) within each group will be assessed by paired Student *t* test or Wilcoxon signed-rank test. Differences in study outcomes between groups (control versus experimental) post intervention will be analyzed using unpaired Student *t* test or Mann–Whitney *U* test. An intention-to-treat analysis will be performed by including all the participants regardless of adherence to the study protocol. The last-observation-carried-forward method will be utilized to minimize the number of missing values due to dropouts. Statistical significance will be set at the *P* <0.05 level (two-tailed) for all analyses. The Consolidated Standards of Reporting Trials statement 2010 flow diagram will be used to explain the stages of the randomized controlled trial

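### Stratification by RA or OA is left conditional on recruitment, and the stated between-group tests omit diagnosis whichever way allocation is done

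*Protocol article*

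**What the plan says.** All references are to the protocol article.

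- **Sample size calculation:** the article states: "In this pilot trial, a formal sample size calculation was not carried out". It nevertheless fixes the total at 30: "Thirty participants [31] will be recruited and allocated into two groups throughout the data collection period".
- **Randomization:** the list is described first: "the two groups will be generated with equal allocation ratio (1:1) by referring to a computer-generated group allocation". On diagnosis, the section then says that "randomization will also be stratified, RA or OA condition wise, depending upon the number of participants being recruited". No threshold, decision time or decision-maker is given for the condition.
- **Randomization, concealment:** the stated method is that "allocation will be concealed in sequentially numbered, opaque, sealed envelopes and will be opened only after the participant details are written on the envelope". A staff member outside the trial generates the sequence and keeps it until the study ends.
- **Baseline visit:** diagnosis is recorded before allocation.
- **Statistical analysis plan:** "Differences in study outcomes between groups (control versus experimental) post intervention" are tested with an unpaired t test or a Mann–Whitney U test at the two-sided 0.05 level. Neither diagnosis nor any other covariate enters.

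**The concern.** Participants enter one at a time and each takes the next envelope in a numbered series. Whether there is one series or two has to be settled before the first envelope is filled. Since the total is already 30, what recruitment will reveal is the RA/OA mix, and that is known only at the end. As worded, a reader cannot tell whether the trial will be stratified.

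The analysis does not resolve this. Diagnosis is the only stratification factor named, it is known for everyone at baseline, and the stated tests ignore it. Two different consequences follow, one for each possible design. If allocation is not stratified, the arms may differ in diagnosis mix by chance and the unadjusted estimate carries that difference. If it is stratified, the unadjusted test counts between-diagnosis variation as noise although the allocation has removed it from the treatment contrast. Either matters for a trial whose purpose is a preliminary estimate of effectiveness.

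**Working it through.** The protocol gives no power, SD or effect figure, so there is none of its own to reproduce.

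**Inputs.** From the protocol: N = 30, 1:1 allocation (15 per arm), two-sided 0.05, unadjusted test on post-intervention values. Assumed: the number K of RA participants (6 to 20 of 30) and the RA–OA difference on the outcome, δ (0 to 1.5 within-diagnosis SDs).

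**Case 1: allocation not stratified.** The number of RA participants in one arm, X, is hypergeometric (30 people, K with RA, 15 drawn), and the gap between arms is |2X − K|. The gap has the same parity as K.

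| K (RA of 30) | Event | Probability |
|---|---|---|
| 6 | gap ≥ 4 | 0.169 |
| 10 or 20 | gap ≥ 4 | 0.245 |
| 11 | gap ≥ 4 (in effect ≥ 5) | 0.128 |
| 12 | gap ≥ 4 | 0.264 |
| 15 | gap ≥ 5 | 0.143 |

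A gap g shifts the unadjusted mean difference by (g/15) × δ:

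- g = 4: 4/15 × 0.5 = 0.13 SD; 4/15 × 1.0 = 0.27 SD.
- g = 5: 5/15 × 0.5 = 0.17 SD; 5/15 × 0.8 = 0.27 SD.

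Over repeated randomizations these shifts average to zero and are part of the sampling error. Simulation (60,000 trials per scenario; K = 10, 14, 20) gives type I error of 0.049 to 0.052 for the unadjusted t test at every δ.

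**Case 2: allocation stratified, analysis unadjusted.** The true standard error of the mean difference is √(2/15) = 0.365 SD whatever δ is, because diagnosis is balanced. The t test instead estimates a within-arm variance of about 1 + 30·p(1 − p)·δ²/28, with p = K/30. For K = 10 and δ = 1.0 this is 1 + 30 × (1/3)(2/3)/28 = 1.238, so the expected SE is about √(2/15 × 1.238) = 0.406, some 11% too large. The simulated mean SE is 0.403.

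Simulated results over K = 10, 14 and 20, with power at a 1.06 SD effect (the effect that 15 per arm detects with 80% power):

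| δ (assumed) | Mean unadjusted SE | Type I error | Power |
|---|---|---|---|
| 0 | 0.362 | 0.049–0.050 | 0.80 |
| 0.5 | 0.372–0.374 | 0.043–0.045 | 0.78 |
| 0.8 | 0.388–0.392 | 0.035–0.037 | 0.75–0.76 |
| 1.0 | 0.403–0.407 | 0.028–0.031 | 0.72–0.73 |
| 1.5 | 0.449–0.458 | 0.014–0.016 | 0.63–0.65 |

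**With diagnosis in a linear model.** Under stratified allocation, type I error is 0.049 to 0.051, the mean model SE is 0.362, and power is about 0.80 at every δ. Under unstratified allocation, power is 0.78 to 0.79 at every δ, against 0.71 to 0.72 for the unadjusted test at δ = 1.0. If δ = 0 in that case, adjusting costs about 2 points of power (0.78 against 0.80).

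**The case against.** The strongest case on the other side is that this is a small pilot without a formal sample size, that a simple test is adequate for a preliminary estimate, and that neither design inflates false positives. All of that stands, and it limits the weight. The clause can also be read as saying only that stratum sizes will depend on recruitment. That reading is possible, but the sentence as written makes stratification itself sound optional, so it needs rewording anyway.

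The documents never say that diagnosis predicts the outcome. It is inferred from the choice of stratifier and from the partly different joint patterns described in the Background, and its size is an assumption. The Discussion argues that the DASH range makes participants homogeneous regardless of arthritis type. That concerns self-reported level, not the performance-based primary test, so it does not settle the matter.

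A reader might infer more than the text supports:

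- **A list rebuilt during the trial, with weaker concealment.** Nothing describes this. The stated arrangement is that "allocation will be concealed in sequentially numbered, opaque, sealed envelopes", with the sequence held by someone outside the trial.
- **Reliability figures as evidence of prognosis.** Test–retest coefficients "in 20 individuals with RA ranged from 0.53 to 0.96", against 0.7 to 0.96 in 26 with OA. The ranges overlap, come from small samples, and describe repeatability, not level or change.
- **Both harms at once.** They belong to different designs. Without stratification the unadjusted standard error is valid on average; with it, balance is obtained.

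The imbalance shifts worked out above are also unlucky draws, each smaller than one standard error (0.365 SD).

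**Conclusion.** The point holds as a defect of specification with a modest statistical cost. The stratification rule cannot be carried out as worded for a pre-generated envelope series, and the stated analysis omits the one factor the protocol proposes to stratify on.

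If allocation is unstratified, the test is valid on average but an RA/OA gap of 4 or more arises with probability of roughly 13% to 26%, depending on the mix. If it is stratified, the test is conservative, with type I error about 0.04 to 0.03 and power about 0.78 to 0.72 instead of 0.80, for an assumed RA–OA difference of 0.5 to 1.0 SD. If RA and OA do not differ on the outcome, neither design loses anything. The size therefore rests on an assumed diagnosis effect and an assumed mix. For a 30-person pilot the weight is moderate to low.

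**What to change.** 1. **Allocation.** Remove the conditional clause. Commit before the first allocation to two concealed lists, one for RA and one for OA, each with its own numbered envelope series. Use randomly varying block sizes and avoid blocks of 2, where the second assignment follows from the first.
2. **If allocation has already begun** (the article gives the trial status as ongoing), leave the existing list unchanged and make only the analysis change.
3. **Analysis.** In either case include diagnosis in the between-group comparison: as a covariate in a linear model or, where a rank test is used, by a diagnosis-stratified rank test (van Elteren), since the Mann–Whitney test takes no covariate.

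The cost is a second envelope series, a possible imbalance of one or two people in total arm size, some predictability within small blocks when staff delivering the interventions know earlier assignments, and one degree of freedom. No new data are needed, because diagnosis is already recorded at baseline.

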### Home program training sessions

Based on clinical experience and pilot data, three training sessions for approximately 45 to 60 minutes each time are essential before initiating the home program. Each participant from both groups will attend the sessions within 7 to 10 days after the baseline visit.

Care will be taken to ensure that each participant is educated well to perform their respective interventions and to record pain and stiffness levels using computer software. The experimental group will also be shown how to instrument personalized objects with the mouse and how to access the computer games. All participants will be given an opportunity to discuss, clarify and ask questions regarding their home program.

The control group will be provided with medium-resistance therapeutic putty (85 g) and a dumbbell as home program accessories. The experimental group will be provided with an equipment package that includes a motion-sense mouse, a set of personalized objects and commercial computer games, and a few accessories such as Velcro strips and wooden dowel for object instrumentation. Both groups will be provided with software for use on their home computer to record and store pain and stiffness levels using separate 0 to 10 numerical verbal rating scales, before and after each exercise session.

### Six-week home program

After the training sessions, both groups will be provided with a written protocol of their home program. The protocol will include clear description of each exercise/manipulation to be performed, number of repetitions (control group) or minutes of play (experimental group) and the number of sessions per week.

The control group will perform the conventional hand exercise program, and the experimental group will perform the task-oriented training with personalized objects, selected by the clinical judgment drawn from the baseline findings.

At the start of the home program, the study staff will attend each participant’s home to ensure proper set-up of their respective intervention. A week later, both groups will be contacted through telephone calls or electronic mails to assess their ability to manage the home program. Both groups will be asked to perform their exercises four times per week for 6 weeks. The pain and stiffness files can be saved to a USB flash drive or sent as an email attachment for regular monitoring by the study staff.

Treatment progression or modification will be made for both groups every 2 weeks depending on individual needs and abilities. When no increased symptoms (assuming a benchmark score >5 in the pain and the stiffness scales) are reported during or after exercises, progression will be followed as in Table 1. In cases of any symptoms being reported, the treatment parameters will be modified by reducing the number of repetitions or minutes of play. Any occurrence of increased pain or stiffness continuing over 1 week would be recorded as an adverse event. The intervention will be discontinued and the participant will be referred to his/her general practitioner.

**Table 1 T1:** Treatment progression guidelines for both groups

**Group**	**Progression goals**	**0 to 2 weeks**	**3 to 4 weeks**	**5 to 6 weeks**
Control group	Number of repetitions of each exercise	5	8	12
Experimental group	Personalized objects	3 to 4	4 to 5	5 to 6
Both groups	Strengthening (60 to 70% of one repetition maximum	1 set ×10 repetitions	1 set ×15 repetitions	1 set ×20 repetitions
Both groups	Exercise duration	15 minutes	20 minutes	25 minutes

The study staff providing the interventions will maintain a record of treatment sessions, exercises prescribed and their progression for each participant. Information on adverse symptoms would include severity, duration and the appropriate treatment modifications done.

A final session to evaluate the primary and secondary study outcomes will be conducted at the end of the 6th week of the home program.

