**Figure 1 F1:**
[figure not shown]
**Instrumentation of objects.** (**A**) A coffee mug is instrumented with the motion sense mouse using Velcro strips. (**B**) A turning knob is instrumented with the mouse using a wooden block, dowel, rubber pad and Velcro strips.

Common objects of daily life have different physical, functional and ergonomic properties. Taking advantage of these properties, objects can be selected to train dexterity, graded mobility in metacarpal phalangeal, interphalangeal and wrist joints, or strengthen finger and wrist muscles. A framework (Figure 2) has been developed for selecting therapeutic objects for specific therapeutic values. The application allows manipulation of objects of any shape (cylindrical, spherical, conical and rectangular) or size (small, medium and large). A wide range of small to large objects can be used to train dexterous functions involving the use of two, three or four fingers or the whole hand, wrist and forearm in order to improve task accuracy, precision and movement quality/efficiency. Training of such skills are expected to emulate many daily functional activities such as holding/manipulating fine, medium and large objects, and cylindrical or spherical objects, turning a door key, doing up buttons, or pulling up/down zippers during dressing. A bottle cork, salad tongs, door knob, key, and fine beads are a few objects that can be selected to train fine manipulations. Large-sized balls, large–medium-sized scissors, a coffee mug, large–medium–small diameter paper rolls and sponge foam cylinders can be selected for gross manipulations. In addition to dexterity, strength training needs to be included because hand strength is also needed to perform many daily tasks requiring a strong grip, such as carrying heavy items, opening tight jars and turning large knobs.

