##### Therapeutic values: strengthening

6. Object selected: half-filled jug

Method: the jug is held with the whole hand around the handle and the task requires tilting the jug sideways up or down, simulating pouring activity.

7. Object selected: a dumbbell

Method: a dumbbell held with the whole hand and forearm supinated or pronated can be used for graded strengthening of wrist flexors or extensors (Figure 3D).

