#### Secondary outcome measures

The secondary outcome measures are the DASH questionnaire and an exercise log diary.

The DASH questionnaire, a reliable and valid outcome measure in the arthritis population [40,41], will be used to measure self-reported hand function ability. The DASH has 30 disability/symptoms questions on difficulties in activities of daily living and scores range between 0 and 100. Higher scores indicate severe disability.

A personal exercise log diary will be used to measure exercise compliance. The number of completed exercise sessions out of 24 total exercise sessions in 6 weeks will be calculated. Any adverse symptoms such as an increase in pain or stiffness experienced due to exercising, technical difficulties reported by the participants and the study completion rate will also be documented

A computer-based paddle game with two modes – predictable visual tracking and random play – has been developed to objectively quantify the quality and accuracy of finger hand movements during manipulation of a broad range of common objects independent of physical properties, anatomical requirements and task goal/context [42,43]. For the present study, the tool will be designated as an exploratory outcome measure.

For the predictable visual tracking, predictable, sinusoidal visual tracking (configurable amplitude and frequency) provides a controlled visual input to guide a motor task. An instrumented object will be held by a specific grasp and moved rhythmically in concert with the moving visual target on the computer screen. The position coordinates of the onscreen moving target cursor and the actual object motion will be synchronously logged and saved. The data will be then processed and analyzed using custom analysis routines written in Matlab (The Math Works, Natick, MA, USA).

Quality and accuracy of finger hand movements during tracking will be measured by spatio-temporal accuracy outcomes. Based on the known target trajectory and the user motion, the coefficient of determination will be calculated (Figure 4A). The coefficient of determination determines the overall movement quality of the manipulation task and the values range between 0 and 1. Values near to 1 indicate close fits of the user motion signals with the target cursor motion, and values far from 1 explain the least fit.

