**Figure 5 F5:**
[figure not shown]
**Parsed movements from a random game play.** Outcome measures derived from episodic game play are shown.

The tool is also embedded with two separate numerical verbal pain and stiffness scales. The pain scale ranges from 0 (no pain) to 10 (unbearable) and stiffness from 0 (none) to 10 (cannot move). These scales will appear in sequence on the computer monitor before and immediately after each pre-timed sinusoidal tracking or the random game. Participants will be asked to verbally rate their pain and stiffness intensity before and after each manipulation task. The study staff record them, and they will be automatically saved along with the user motion data.

The tool will be used to evaluate quality and spatio-temporal accuracy during four manipulation tasks with objects such as a salad tongs, a small bead, jug and a turning knob. These objects are selected to represent a diverse range of manipulation tasks needing different functional requirements of handling. Note: in order that there is no practice effect, these four objects will not be included for the experimental group. Our previous pilot work has reported that the jug and salad tongs were difficult to manipulate in people with RA or OA. So these two manipulation tasks will be evaluated in predictable tracking mode with a duration of 30 seconds. Skill and efficiency of the other two manipulations will be evaluated while playing the random game for 90 seconds. Evaluation of all four tasks may take approximately 7 to 10 minutes.

The measures derived from both game modes of the computer-based hand assessment tool are as follows: predictable tracking – task performance (coefficient of determination), spatio-temporal accuracy measures (temporal accuracy, amplitude consistency), pain and stiffness intensity; and episodic (random) game – success rate (number of target hits), movement skill (average motor initiation time, average motor response time), movement efficiency (movement path length), and pain and stiffness intensity.

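### The practice-effect rule protects only the exploratory tool; nothing keeps the objects of the primary test out of experimental-arm training

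*Protocol article*

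**What the plan says.** All references are to the protocol article.

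- **The safeguard.** Under Secondary outcome measures (text after Figure 5), the computer-based tool uses "four manipulation tasks with objects such as a salad tongs, a small bead, jug and a turning knob". The protocol adds that "in order that there is no practice effect, these four objects will not be included for the experimental group". The same section states that "the tool will be designated as an exploratory outcome measure".
- **The primary outcome.** Under Primary outcome measure, the Arthritis Hand Function Test covers grip and pinch strength, a peg-board, applied dexterity and applied strength. Applied dexterity is a total time over tasks with shoelaces, buttons, safety pins, coins, and a knife and fork. Applied strength uses soup cans on a tray and "the volume (ml) of water lifted in a pitcher". No rule there limits which of these objects may be trained.
- **Choice of training objects.** Under Six-week home program, the experimental arm uses "personalized objects, selected by the clinical judgment drawn from the baseline findings". Under Baseline visit, the first assessment covers daily-living problems, observed object handling, and "assessment of primary and secondary study outcomes".
- **The object list.** Under Experimental group, the seven listed objects are presented as examples. One is a half-filled jug, for which "the task requires tilting the jug sideways up or down, simulating pouring activity". The Background text after Figure 1 expects training to emulate activities such as "turning a door key, doing up buttons, or pulling up/down zippers during dressing".
- **The control arm.** Under Control group, the programme is a fixed set of finger and wrist movements plus strengthening with putty and a dumbbell.

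**The concern.** The protocol accepts that training on an assessed object can improve the score through practice on that object. It applies this principle to the lowest tier of outcome and leaves the highest tier uncovered.

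If an experimental participant trains for six weeks with an object that is also part of the primary test, a better score on that item may reflect familiarity with the item rather than better hand function. Hypothesis 1 claims better hand function in general. The control arm has no comparable opportunity, so any such gain would enter the between-group difference. Assessor blinding does not help, because what changes is the participant's own performance and not the way it is scored. In a pilot whose purpose is a preliminary estimate of effectiveness, a one-sided bias in that estimate could carry into the planning of a larger trial.

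**Working it through.** The protocol gives no effect size, standard deviation or power, and says that no formal sample size calculation was done. There is no design figure to reproduce, so the check is mainly a comparison of sections.

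**Step 1. Scope of the rule.** It names salad tongs, a small bead, a jug and a turning knob. All four belong to the exploratory tool. It contains no reference to the Arthritis Hand Function Test.

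**Step 2. Can a primary-test object enter training?** The listed objects are examples, so the set is open. Selection rests on clinical judgment from the baseline findings. Read together, the Baseline visit and Six-week home program sections allow the primary test results to be among those findings. Nothing in the text excludes them.

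**Step 3. Is the exposure one-sided?** Objects are chosen only for the experimental arm, after randomization, so whoever chooses them knows the allocation. The control list has no everyday-object manipulation. The exposure is one-sided.

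**Step 4. Which primary components are open to it?**

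| Component in the analysis plan | Everyday objects in the test? | Open to one-arm rehearsal? |
|---|---|---|
| Grip strength | No | No; both arms do strengthening |
| Peg-board dexterity | Pegs only | Possibly |
| Applied dexterity | Laces, buttons, pins, coins, knife and fork | Yes in principle, though several are hard to fit with a motion mouse |
| Applied strength | Cans on a tray, water pitcher | Yes in principle |

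**Step 5. Actual overlap with the listed objects.** Key, bottle cap, ball, plate or board, drinking glass and dumbbell match no test item. The half-filled jug resembles the pitcher. It is tilted in training, whereas the test records the volume lifted. The jug is also one of the four barred objects, so its place in the training list contradicts the rule.

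**Step 6. Illustration only.** Suppose there is no general benefit, but rehearsal shifts the experimental-arm mean on one analysed measure by d standard deviations. These d values are assumptions. Inputs from the protocol are 30 participants allocated 1:1 (15 per arm if exactly equal) and two-sided 0.05. The noncentrality is d × √(15/2) = 2.739d, with 28 degrees of freedom.

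| Assumed d | Noncentrality | Chance of a significant result favouring the experimental arm |
|---|---|---|
| 0 | 0 | 2.5% |
| 0.2 | 0.55 | 7.6% |
| 0.3 | 0.82 | 12.2% |
| 0.5 | 1.37 | 26.2% |

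Objects are personalized, so d is an average over the arm. If only a fraction of participants train with an overlapping object, d is that fraction times the individual gain. It shrinks again when the item is only part of a component. The table shows how the error rate would respond to a shift. It does not estimate the shift.

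**The case against.** The strongest reply has four parts.

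1. **Little overlap is visible.** Only the jug resembles a test item, the existing rule already bars it, and tilting a jug to steer a cursor is not lifting a measured volume. This stands. The jug cannot serve as evidence that the primary test will be rehearsed.
2. **Two tempting inferences go too far.** A reader might infer that staff will choose objects to match the items on which a participant scored worst. The protocol does not say so. It does not name the primary test as a basis for selection, and it lists daily-living problems and handling observations separately, which are a natural basis. A reader might also infer that buttons will be trained. The Background names doing up buttons as a function to be emulated, not as a training object. Objects must also carry the motion mouse, which makes lacing, pinning or posting coins hard to rehearse as tested.
3. **Details may lie elsewhere.** The selection framework is in Figure 2, which is not shown, and may narrow the choice. This also stands, and nothing is held against the plan on that account. The text that is shown sets the practice-effect rule explicitly and limits it to four objects.
4. **Gains on daily tasks are the aim.** Task-oriented training is meant to transfer to daily life, so a ban on every everyday item would partly change the intervention. This limits how far the fix should go. It does not remove the point, because the protocol's own rule already separates practice on an assessed object from general improvement.

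**Conclusion.** The point holds as a gap in a safeguard. The protocol's practice-effect rule covers an exploratory tool and leaves the primary outcome without equivalent protection, while overlap is permitted in the experimental arm only. The exposure lies in applied dexterity and applied strength, two of the four primary-test components named in the Statistical analysis plan section, with the peg-board a lesser possibility. The direction would favour the new programme.

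The documents do not support saying that overlap will occur or that the primary comparison is biased by any particular amount. They give no rehearsal effect and no standard deviation, and they do not state how long any one object is used. The illustrated percentages depend entirely on the assumed shifts. This is a worthwhile, inexpensive improvement and not a flaw that invalidates the design. Separately, the training list and the practice-effect rule disagree about the jug and must be reconciled.

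**What to change.** 1. **Extend the rule.** Add a sentence to the practice-effect note so that objects used in Arthritis Hand Function Test items are not used as experimental training objects. State how near-copies are treated, and reconcile the jug entry in the training list with the existing bar. The rule should concern the test's own objects, not everyday objects in general, so that the task-oriented aim is kept.
2. **Fix the basis for selection.** State in the Six-week home program section that objects are chosen from the daily-living problems and the object-handling observation already recorded at baseline, and not from the primary test scores.
3. **Make overlap visible.** Use the existing per-participant record of exercises prescribed to list any trained object that matches a test item, and report the affected component with and without that item. For applied dexterity, which is a total time, this requires the time for each task to be kept.

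**Cost.** Two sentences and one sensitivity table. The choice of objects becomes slightly smaller, a modest loss given the wide range that the Background describes.
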